### Qualitative Analysis

Qualitative analyses will be guided by a thematic analysis and use a team approach to enhance rigor and reproducibility [45]. Analytic steps will include the following: (1) after each interview, interviewers will document field notes including emerging topics for further exploration; (2) verbatim transcripts will be entered into MAXQDA qualitative software (VERBI Software GmbH); (3) we will develop a preliminary codebook to include predetermined deductive codes related to the domains of interest, and inductive codes that emerge; (4) analysts will code a subset of transcripts and compare coding, with differences discussed in team meetings until consensus is reached; similarities and differences across transcripts will be examined, revising codes accordingly. We will cease developing new codes when no new themes are seen; (5) analysts will proceed to individually code full transcripts and meet weekly to troubleshoot concerns and; (6) properties and dimensions of salient themes will be summarized and interpreted in detailed analytic memos.

## Results

Phase 1 (development) of Weyera research activities began in January 2025 and was completed in June 2025. The data collection for the phase 2 pilot implementation trial began in September 2025 and is expected to be completed in April 2026. Final results are anticipated in summer 2026.

## Discussion

### Expected Findings

The trial is well positioned to make a significant contribution by demonstrating that the Weyera intervention is feasible, acceptable, and safe among Ethiopian and Eritrean immigrant youth. There are currently no published studies of interventions that specifically target the mental health needs of Ethiopian and Eritrean youth in the United States. Given this research gap, this trial will provide evidence on whether a community-based, peer-led mental health intervention can begin to address the mental health needs of this community. Studies involving different immigrant groups indicate that peer-led mental health interventions are both acceptable and feasible, and these programs can improve self-rated anxiety and happiness levels, depressive symptoms [17], and psychosocial functioning while decreasing social isolation [16]. This trial builds on this evidence to specifically develop an intervention for and with Ethiopian and Eritrean immigrant youth.

### Limitation and Future Directions

This randomized wait-list control trial is designed to minimize bias. Beyond the study team, participants remain unaware of their specific group assignment; they are only notified of the start dates for their respective group sessions. Sessions for both the immediate and wait-list groups are designed and implemented identically. Nevertheless, this methodology does not entirely eliminate potential selection bias, given the inherent challenges associated with this study design, in which the wait-list group may be prone to higher dropout rates due to the interval between enrollment and the start of the intervention. Furthermore, varying expectations among participants may affect their motivation to fully engage with the intervention following the waiting period. In addition, the presurvey and postsurvey measures are self-reported by study participants, which can introduce biases due to reduced accuracy and potential social desirability bias.

Upon the conclusion of this trial, in collaboration with the CBOs, the team will conduct webinars to present our qualitative and quantitative findings. In addition, further dissemination will include scientific and academic journal publication and conference presentations. Building upon the findings of this research, the subsequent objective of the project is to undertake a statistically powered trial designed to evaluate the efficacy of the intervention in addressing the mental health needs of Ethiopian and Eritrean immigrant youth.

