### Study Design

#### Overview

Phase 1 of this study, Weyera’s intervention development approach is guided by the intervention mapping framework [19], a proven, repeatable method for systematically creating interventions based on theory. In phase 2, we will conduct a wait-list control trial. Participants will be randomized upon enrollment to either an immediate intervention group or a delayed intervention (wait-list control) group, in which they will receive the intervention after a 2-month waiting period. Randomization will be done using the National Institutes of Health clinical trial randomization tool [24] to randomly generate a sequence. At enrollment, participants are assigned a study ID. Participant study ID will be entered into the online randomization software to assign participants into arm 1 or arm 2. A coin flip will then be used to designate one arm as the intervention and the other as the wait-list control group. Study allocation will be concealed from study participants and will only be limited to study staff. Participants are notified of their study group start date and all subsequent sessions. This study followed the CONSORT (Consolidated Standards of Reporting Trials) extension for pilot and feasibility trials, the TIDieR (Template for Intervention Description and Replication) checklist, and the SPIRIT (Standard Protocol Items: Recommendations for Interventional Trials) guidelines (Checklists 1-3).

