
Participants will attend a 2-hour group session once per week for 8 weeks. The first and final sessions are designed to be delivered in person, while the remainder is to be delivered via Zoom videoconference. A total of 2 or 3 trained PFs will lead sessions. The structure, duration, and length of the program were designed by the study team together with the YAB and also reflect previous group interventions developed for other immigrant groups [15,16,18]. Sessions will include psychoeducation, engaging, interactive activities (eg, case-scenario discussions and trivia games), and practice of coping skills (Table 1). Participants will complete a session evaluation form each week and receive US $25 payment on an electronic gift card. All participants will be provided with a mental health resource guide featuring affordable services verified and compiled for Ethiopian and Eritrean youth in Atlanta. After completing the program, participants will receive links to follow-up surveys at 2, 4, and 6 months, and a subset will take part in qualitative interviews.

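### Participants are said to be unaware of their group, but start time is the only difference between arms and they are told it, so the trial is not blinded and this cannot count as a bias protection

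*Protocol article*

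**What the plan says.** The claim appears twice. The Overview under Study Design says: "Study allocation will be concealed from study participants and will only be limited to study staff". Limitation and Future Directions repeats that "participants remain unaware of their specific group assignment; they are only notified of the start dates for their respective group sessions". There it directly follows the statement that the randomized wait-list design is intended to keep bias low, so it reads as one of the reasons.

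The same document describes what participants are told and how the arms differ:

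- Study Design, Overview: "Participants are notified of their study group start date and all subsequent sessions".
- The same section describes the delayed group as one "in which they will receive the intervention after a 2-month waiting period".
- Limitation and Future Directions: "Sessions for both the immediate and wait-list groups are designed and implemented identically".
- Participant Experience: "Participants will attend a 2-hour group session once per week for 8 weeks".

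On measurement, Data Collection has participants fill in the surveys themselves, and the limitations section accepts that "the presurvey and postsurvey measures are self-reported by study participants". Statistical Analysis treats the mental health outcomes as exploratory, to be examined with linear mixed models. Feasibility, acceptability and safety are handled descriptively.

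**The concern.** The article claims a property that its design cannot have. If content is identical and only timing separates the arms, the start date carries the allocation, and attendance confirms it.

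This matters because the outcomes compared between arms are the participants' own ratings of mood, anxiety, resilience, stigma, coping and the like. Someone who knows that they have just completed a support programme, or are still waiting for one, may answer differently for that reason alone. A reader who takes the unawareness statement at face value would think the arm comparison is protected against this. The article lists self-report and social desirability as limitations, but it never says that participants are unblinded and never links their answers to knowing what they have received.

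**Working it through.** The plan states no figure on this point, so the check compares its statements and adds simple schedule arithmetic.

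**1. What separates the arms.** Both Overview sections (Study Design and Phase 2) define them as immediate start or start after a 2-month wait. The limitations section says the sessions are otherwise the same. Timing is therefore the whole of the allocation.

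**2. What participants learn.** They are told the start date and all later session dates, which is the one fact that distinguishes the arms. All that can still be withheld is the name of the group.

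**3. What participants experience.** Eight sessions of 2 hours give 8 × 2 = 16 hours of group contact over about 8 weeks. The wait is 2 months, or 2 × 52/12 ≈ 8.7 weeks. An immediate group that starts on time can therefore finish before the delayed group begins.

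**4. What this means at the surveys.** The document supports two readings of the follow-up clock.

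| Reading | Source | Immediate arm at month 2 | Delayed arm at month 2 |
|---|---|---|---|
| Counted from baseline or group start | Data Collection | up to 8 sessions, 16 h | 0 sessions, 0 h |
| Counted from the end of the programme | Participant Experience | 8 sessions, 16 h | 8 sessions, 16 h |

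On the first reading, the 2-month contrast sets people who know they have been treated against people who know they have not. On the second, both arms have completed the programme by each follow-up, so knowledge of treatment would act mainly on change from baseline and less on the arm contrast. On neither reading is a participant unaware of having received the intervention. The blinding statement fails either way; only the place where bias could enter changes.

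**5. Concealment and blinding.** Allocation concealment means that the next assignment cannot be foreseen before it is made. Blinding means that it stays unknown afterwards. The Study Design text uses the language of the first to claim the second.

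**6. Which outcomes are exposed.** Table 2 has 13 rows, all completed by participants. One row asks about use of the coping techniques practised in the sessions, so attendance may influence those answers directly. The feasibility measures in Statistical Analysis (recruitment, staff effort, screening, enrolment proportion, missed sessions) do not rest on these ratings. Safety is a tabulation of adverse events.

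**The case against.** The strongest reply is that the statement may mean only that nobody is told a group label, and that a date need not reveal the label. Participants accrue in groups of 16, so immediate starters may also wait, and the article does not say whether consent describes the two-arm design. This stands for the period before sessions begin: how much a date alone reveals cannot be established. It does not rescue the claim, because attending or not attending eight sessions shows whether treatment has been received.

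A second reply is that the limitations paragraph is not one-sided. It goes on to name selection bias, differential dropout, varying expectations, self-report inaccuracy and social desirability. That is correct, and the paragraph as a whole should not be called wrong. What fails is one supporting reason and one omission: the expectations sentence concerns engagement with the programme, not how surveys are answered.

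A reader might also treat the warning that "the wait-list group may be prone to higher dropout rates due to the interval between enrollment and the start of the intervention" as an admission that participants know their arm. It does not go that far. A long wait can cause dropout in people who have never heard a group name.

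Finally, it may be tempting to infer that inflated pilot estimates would set the size of the later full trial. The document does not support this. Sample Size and Power already calls effect sizes from small pilots unreliable and bases the 60 participants on other grounds, and no section proposes carrying the estimates forward.

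**Conclusion.** The unawareness claim is wrong as written in both places, and it cannot support the statement that the design limits bias. Participants know whether they have had the sessions. That the trial is unblinded after assignment is an inference, since the document does not use the term, but it follows from the document's own description of the arms.

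The reach is limited. The exploratory between-arm comparisons of the 13 self-reported rows are affected. The descriptive feasibility and safety aims are largely not. Acceptability is summarised from post-session satisfaction ratings and does not depend on a masked arm contrast.

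Bias toward apparent benefit is the likely direction for an unblinded wait-list comparison of self-ratings. This is general reasoning: the document does not show that every such influence runs that way, and it gives no basis for a size. How strongly the arm contrast is exposed also depends on which reading of the follow-up clock applies.

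**What to change.** In Study Design (Overview) and in Limitation and Future Directions:

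- State that participants and facilitators are not blinded after assignment.
- Use *concealed* only for the period before assignment.
- Remove participant unawareness from the reasons given for low bias.
- Add that the exploratory between-arm comparisons of self-reported outcomes may be affected by knowledge of treatment received, probably toward benefit and by an unknown amount.

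The results report should carry the same description. No procedure, sample size or analysis changes. The article reports that analysis had not started as of March 2026, so the correction can be in place before any comparison is read. The only cost is a less favourable stated protection against bias.
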